#### Part 2: effect of blood pressure on mTc-MEP characteristics in spinal surgery

After induction of anesthesia and positioning the patient in prone position, and before the start of spinal surgery, the propofol infusion will be adjusted to achieve a target pEEG value of 40. After induction of anesthesia, to achieve a pEEG value of 40, the MAP is often 60 mmHg or lower. A slow intravenous infusion of noradrenaline will be started to slowly increase the MAP. Every 2 min, while increasing the infusion rates, mTc-MEPs will be performed for the left and right TA, GAS and AH hallucis muscles (Fig. 2). At MAP levels of 60 mmHg, 80 mmHg and 100 mmHg an mTc-MEP threshold will be measured for the abovementioned muscles. The noradrenaline infusion rate will be adjusted to achieve a gradual MAP increase over 30 min, until the MAP is approximately 100 mmHg. MAPs will be measured continuously using an invasive arterial cannula, which will have already been inserted for clinical care. In the event that the MAP after induction is greater than 60 mmHg but lower than 80 mmHg, we will accept that value, and use noradrenaline as necessary to increase the MAP to 100. In the event that the MAP is spontaneously > 100 mmHg immediately after induction, the patient will be withdrawn from the study, and further care passed on to the responsible anesthesiologist.

**Fig. 2 Fig2:**
[figure not shown]
Schematic overview study design part 2: effects of blood pressure on mTc-MEP characteristics in spinal surgery. *MAP* mean arterial pressure, *mTc-MEP* muscle recorded transcranial electrical stimulation motor evoked potential

Due to the inadequacy of blood pressure to predict tissue perfusion directly, this study will also collect other calculated hemodynamic parameters generated by an EV1000 monitor consisting of cardiac output, pulse pressure variation and stroke volume variation.

In order to determine if a combination of MAP, with pEEG and/or propofol concentration (estimated effect-site concentration, or estimated or measured plasma concentrations) better predict mTc-MEP characteristics than the MAP on its own, in total three blood samples will be taken (10 ml per blood sample) at MAP values of approximately 60, 80 and 100 mmHg, to measure the propofol plasma concentrations. Propofol Ce values and pEEG values will be collected directly after each mTc-MEP measurement as well. See Table 1 for the participant timeline.

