###### Hypothesis

A Higher MAP will:

Reduce the threshold voltage required to evoke an mTc-MEP.Increase the mTc-MEP amplitude and the mTc-MEP AUC.

A range of alternative hypotheses will also be explored. These include:

There is a biphasic relationship between MAP and mTc-MEP amplitude and AUC (with an initial improvement and a subsequent decrease at higher noradrenaline doses and MAP values).The MAP at which optimal mTc-MEP amplitudes and AUCs are found is age-dependent.

#### Secondary objective 1

To determine if a combination of MAP, with pEEG and/or propofol concentration (estimated effect-site concentration, or estimated or measured plasma concentrations) enables better prediction of mTc-MEP characteristics than the MAP on its own.

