##### Secondary outcome

For the secondary outcome, additional terms for pEEG and propofol concentrations (effects site and blood concentration) will be added to the fixed effects structure of the model specified for the primary outcome. The specification of the random effects structure and the residual covariance structure will not change.

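### In Part 2, measured plasma propofol exists at about 3 of 15–16 MEP times, so for amplitude and AUC the single extended model uses about a fifth of the data and is not like-for-like with a MAP-only model fitted to all of it

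*Protocol article*

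**What the plan says.** All references are to the protocol article.

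- **MEP schedule (Study procedures, Part 2).** "Every 2 min, while increasing the infusion rates, mTc-MEPs will be performed for the left and right TA, GAS and AH hallucis muscles". The ramp length is also given: "The noradrenaline infusion rate will be adjusted to achieve a gradual MAP increase over 30 min, until the MAP is approximately 100 mmHg". Threshold voltage is determined only at MAP 60, 80 and 100 mmHg.
- **Plasma sampling (same section, below Fig. 2).** "in total three blood samples will be taken (10 ml per blood sample) at MAP values of approximately 60, 80 and 100 mmHg".
- **Other predictors (same place).** "Propofol Ce values and pEEG values will be collected directly after each mTc-MEP measurement as well".
- **Objective (Part 2, Secondary objective 1).** The question is whether MAP combined with pEEG and/or propofol concentration predicts MEP characteristics better than MAP by itself. The concentration may be of several kinds: "propofol concentration (estimated effect-site concentration, or estimated or measured plasma concentrations". The paired hypothesis is that MAP alone does as well as the fuller model.
- **Model (Statistical methods, Part 2).** The primary model has continuous MAP as fixed effect, with a random intercept and a random MAP slope. For the secondary outcome, "additional terms for pEEG and propofol concentrations (effects site and blood concentration) will be added to the fixed effects structure" of that model, and "The specification of the random effects structure and the residual covariance structure will not change".

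**The concern.** The secondary model puts three added predictors into one equation, and they are not observed on the same schedule. pEEG and effect-site concentration are available at every MEP. Measured plasma concentration is available at three. A row without a plasma value cannot enter the model as written unless a value is supplied for it, and the article describes no such step.

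The Part 1 secondary model uses nearly the same wording, and there it fits. The MEPs are averaged per stable pEEG level, and one blood sample follows each series. In Part 2 the two schedules diverge, so the same sentence no longer matches the data.

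Three things are at stake for amplitude and AUC:

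- **Lost data.** pEEG and effect-site concentration are estimated from about a fifth of the MEP times, although both were recorded at all of them.
- **Unlike data sets.** The objective compares models. If MAP alone keeps all its rows while the extended model has only the sampled ones, likelihood, information criteria and prediction error describe different data.
- **Direction of the hypothesis.** The expectation is that MAP alone is as good as the fuller model. An imprecise extended fit makes it easier to find no difference, which would look like support.

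**Working it through.** The article states no row count, and its 25 patients per part is a pragmatic number, so there is no stated figure to reproduce. The check is a count of rows, followed by the consequences.

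**Inputs**
- MEP interval 2 min and ramp 30 min (Study procedures, Part 2)
- Measured plasma samples per patient: 3 (same section)
- Patients: 25 (Sample size calculation, Part 2)
- Assumptions: all samples are obtained, each is matched to one MEP time, and unsampled rows are not imputed

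**Rows for amplitude and AUC**
- MEP times per patient: 30/2 + 1 = 16 if time 0 is counted, or 30/2 = 15 if not.
- Patient-times: 25 × 16 = 400, or 25 × 15 = 375.
- Patient-times with a plasma value: 25 × 3 = 75.
- Share kept: 75/400 = 18.75%, or 75/375 = 20.0%. Share lost: 81.25% or 80.0%.
- With the six muscles as separate rows: 400 × 6 = 2,400 falls to 75 × 6 = 450, the same share.

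**Sensitivity**
- One of a patient's three samples missing: 1 − 2/16 = 87.5% lost, or 1 − 2/15 = 86.7%.
- Higher starting MAP with a proportionally shorter ramp (an assumption): a start at 65 mmHg gives 30 × 35/40 = 26.25 min and 14 times, so 1 − 3/14 = 79% lost. A start at 79 mmHg gives 30 × 21/40 = 15.75 min and 8 times, so 1 − 3/8 = 63% lost.

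**Other outcomes and terms**
- Threshold voltage: the MAP levels match the blood samples, so the planned loss is 0% when MAP starts near 60 mmHg.
- Models with pEEG and effect-site concentration only: 0% lost.

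**Comparing fit across different rows.** A log-likelihood sums contributions from the data, so one from 400 patient-times and one from 75 differ even if the added term does nothing. An illustrative simulation showed this. It had 25 patients, 16 times, a random intercept and slope, no true plasma effect, assumed variances and 60 runs, some with convergence warnings.
- MAP on 400 rows against MAP + plasma on 75: the apparent likelihood-ratio statistic averaged about 383 and exceeded 3.84 in every run. The size reflects the assumed variances and the row difference and has no other meaning.
- Both models on the same 75 rows: the average was 0.9 (1 expected), with 3% of runs above 3.84.

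**Precision on the sampled rows.** For evenly spaced MAP from 60 to 100 mmHg, the within-patient sum of squares of MAP is:
- 16 points: 16 × (16² − 1)/12 × (40/15)² = 340 × 7.111 = 2,418
- 3 points: 2 × 20² = 800

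If slopes do not vary between patients, the standard error of the MAP slope rises by √(2,418/800) = 1.74. If between-patient slope variation dominates, the ratio approaches 1. The simulation gave about 1.4, inside that range. The documents do not give the spread of pEEG or effect-site concentration, so no equivalent figure can be given for those terms.

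**The case against.** The strongest reply is that the article never says rows are dropped, that MAP alone stays on all rows, or that likelihoods are compared. Handling of unsampled rows and the comparator data set are often left to the analysis plan, which is not shown. The objective also accepts estimated concentrations and uses and/or wording, so models that lose no rows already lie within its scope.

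Much of this stands, and it limits the point. It does not remove it. The Statistical methods section undertakes to specify the models precisely, names effect-site and blood concentration together, and holds the rest fixed. Table 1 ties blood concentration to the blood samples, so the measured value is the natural reading. That is a specification that does not fit the Part 2 schedule, not only a missing detail.

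A reader might infer more than the documents support:

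- **That the comparison with MAP alone is invalid outright.** It is invalid only if MAP alone is fitted to all rows. Refitting it on the sampled rows is compatible with the text and valid.
- **That every outcome loses about 81%.** Threshold voltage does not.
- **That patients starting above 60 mmHg have only two samples.** The text plans three in total at approximate MAP values and accepts the starting value, which can serve as the first point.
- **That the model is barely identifiable on three points.** Three times per patient give six distinct variances and covariances against four variance parameters (intercept, slope, their covariance, residual). The same-row test in the simulation behaved acceptably. Precision is lost, but the model does not fail.
- **That the random slope should be dropped.** If MAP slopes differ between patients, as the primary model allows, removing it can make the standard error for MAP too small.

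**Conclusion.** The concern holds in a limited form. For amplitude and AUC, the Part 2 secondary model as written can use about 75 of 375–400 patient-times (19–20%). This rests on 15–16 MEP times, three samples per patient, a measured plasma term and no imputation. It needlessly discards pEEG and effect-site data. It also leaves the stated comparison sound only if MAP alone is refitted to the same rows, which the article does not require. Threshold voltage is essentially unaffected.

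The weight is moderate. The objective is secondary, the study is declared hypothesis-generating, and no conclusion about the Part 2 primary objective depends on it. It is still worth correcting before analysis, because the objective is itself a comparison of models.

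**What to change.** Replace the Part 2 secondary-outcome model, for amplitude and AUC, with two separate comparisons:

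- **(a) All MEP rows.** MAP against MAP + pEEG + effect-site concentration, or pump-estimated plasma concentration in place of effect-site.
- **(b) Sampled rows only.** MAP against MAP + measured plasma concentration, with or without the other terms. Fit both models to the identical rows with the same random-effects structure. Keep the random MAP slope where it can be estimated.

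State that fit is not compared between (a) and (b). Threshold voltage can stay under the existing wording, provided both models use the same rows.

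The cost is a change of analysis text and slightly more analysis work. No extra samples or procedures are needed. The downside is lower precision in (b): for the MAP slope, a standard error up to about 1.74 times that on all 16 points, and about 1.4 times in the illustrative simulation.

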### Sample size calculation

#### Part 1:  pEEG

Very little is known about the quantitative relationship between depth of anesthesia, propofol plasma concentration, and mTc-MEP. There are insufficient data available on which to base a sample size calculation. A pragmatic sample size of 25 patients has therefore been chosen. This study should be regarded as a hypothesis-generating study.

#### Part 2: MAP

Although hypotension and hypoperfusion are well known causes of deterioration in mTc-MEP signals, and vasopressors are routinely used to increase the blood pressure when mTc-MEP signals deteriorate, very little is known about the quantitative relationship between vasopressor administration and mTc-MEP. Therefore, there is insufficient data available on which to base a sample size calculation. A pragmatic sample size of 25 patients has therefore been chosen. This study should be regarded as a hypothesis-generating study.

### Recruitment

The surgeon, neurophysiologist and anesthesiologist evaluate whether the patient is eligible for inclusion in one of these studies, following the above mentioned in- and exclusion criteria. Eligible patients will receive a written description of the study at their visit at the outpatient clinic or per mail. All candidates who have been sent the written information and consent form will be visited on the ward before their operation and asked if they have read and understood the information and whether they still have questions about the study. The researcher will ask the patient to sign the informed consent form and then co-sign the consent form.

### Data management

IONM data will be exported from the NIM-Eclipse E4 IONM system (Medtronic BV, The Netherlands) as csv file. After performing simple statistics using python, calculating the peak-peak amplitude and AUC, data will be recorded in Microsoft Access. Anesthesiology data and the neurological examination data will be recorded in a web-based data capture system (REDCAP).

### Statistical methods

For the statistical analyses of both the primary and secondary outcomes, a linear mixed effects model will be used to account for the repeated mTc-MEP measurements. Below, per outcome and per part of the study, the linear mixed effects models will be more precisely specified.

#### Part 1: pEEG

##### Primary outcome

For the primary outcome of part 1, a linear mixed effects model will be fitted in which pEEG target (categorical variable with values 30, 40 or 50) will be included as a fixed effect and a random intercept will be used to account for the between-subject variability in the mTc-MEP measurements. Independent normal distributions with mean zero and constant variance will be used to represent the within-subject errors.

##### Secondary outcome

For the secondary outcome, additional terms for MAP and propofol concentrations (effects site and blood concentration) will be added to the fixed effects structure of the model specified for the primary outcome. The specification of the random effects structure and the residual covariance structure will not change,

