## Background

For complex and high risk spinal surgeries, intraoperative neurophysiological monitoring (IONM) is used, with the aim of detecting and preventing intraoperative neurological injury [1]. For monitoring in spinal surgery, it is advised to monitor both sensory tracts, using somatosensory evoked potentials (SSEPs), and motor tracts, using muscle recorded transcranial electrical stimulation motor evoked potentials, mTc-MEPs [1–4].

The most common warning criterion for possible surgically induced structural neurological injury, is an mTc-MEP amplitude decrease of 50–80% from the baseline value [2, 4–8]. Therefore, an mTc-MEP amplitude decrease of 50–80% warrants immediate exploration of possible causal factors. However, these warning criteria often result in false positive warnings [2]. This can be due to technical issues, but also other factors may influence mTc-MEP amplitudes, including direct effects of anesthetic drugs on neuronal transmission, as well as indirect effects of blood pressure, blood oxygen levels and body temperature resulting in false positive decreases in mTc-MEPs [9–15]. In clinical practice, decreasing the concentration of intravenous anesthetic drugs and elevating blood pressure often help to restore the mTc-MEP amplitude.

It is known that for optimal recording of mTc-MEPs, total intravenous anesthesia (i.e. induction and maintenance of general anesthesia with intravenous infusions of propofol and an opioid) provides more reliable mTc-MEPs than volatile anesthesia (maintenance of anesthesia by administration of a volatile drug through the anesthetic breathing circuit) [16]. However, mTc-MEPs are still very sensitive to the suppressive effects of propofol anesthesia [10, 16–19]. Given the intra- and inter-individual variability in the relationship between blood and effect-site propofol concentrations, and actual clinical effect, it is scientifically important to study the relationship between depth of anesthesia (actual clinical effect) and mTc-MEP characteristics.

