#### Subgroup analysis

Due to the neurophysiological differences at different ages, a subgroup analysis to adjust for age may be performed if applicable.

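### The secondary models give each measured covariate one coefficient, which mixes differences between patients with changes within a patient; this matters most for propofol in Part 1

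*Protocol article*

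**What the plan says.** All references are to the protocol article.

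- **Part 1, primary model.** "pEEG target (categorical variable with values 30, 40 or 50) will be included as a fixed effect". Differences between patients are handled by a patient-level random intercept only.
- **Part 1, secondary model.** "additional terms for MAP and propofol concentrations (effects site and blood concentration) will be added to the fixed effects structure of the model". "The specification of the random effects structure and the residual covariance structure will not change".
- **Part 2, secondary model.** "additional terms for pEEG and propofol concentrations (effects site and blood concentration) will be added to the fixed effects structure". The primary model it extends has continuous MAP, a random intercept and a random MAP slope.
- **Objectives.** Secondary objective 1 in each part asks whether the added covariates improve prediction of mTc-MEP characteristics. The hypotheses are that pEEG alone (Part 1) or MAP alone (Part 2) does as well as the larger model. Part 2 also hypothesises that MAP affects mTc-MEPs more than pEEG does.
- **Intended use.** The Background says that the commonest warning criterion "is an mTc-MEP amplitude decrease of 50–80% from the baseline value", and the stated hope is fewer false positive warnings.
- **Variation between patients.** The Background motivates the study with "Given the intra- and inter-individual variability in the relationship between blood and effect-site propofol concentrations, and actual clinical effect", and the Discussion calls pharmacokinetic variability between individuals large. Patients are enrolled from 12 years with no upper limit. The Subgroup analysis section begins "Due to the neurophysiological differences at different ages" but makes age adjustment optional.

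Statistical methods announces that the models are specified precisely. Neither secondary model mentions centring or patient means.

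**The concern.** Propofol concentration, MAP in Part 1 and pEEG in Part 2 vary both between patients and within a patient. A single term for such a covariate, beside a patient random intercept, estimates a blend of two quantities: how the mTc-MEP changes when the covariate changes in one patient, and how patients with higher average values differ from patients with lower ones. The blend equals the within-patient effect only if the two slopes coincide.

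The Part 1 design makes the between-patient share large for propofol. Every patient is titrated to the same pEEG targets, and the target is in the model as a category. That removes much of the within-patient variation in propofol, while differences between patients in the propofol needed to reach a target remain. MAP in Part 1 may lie anywhere from 70 to 100 mmHg (Anesthetic management), so it too can differ between patients. A trait linked to both the covariate and mTc-MEP size, such as age, then enters the coefficient.

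At stake is what the coefficient is taken to mean. A monitoring team judging a fall from the patient's own baseline needs the within-patient slope. A blended coefficient can invent one, or cancel a real one.

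**Working it through.** The plan has no figure to reproduce: 25 patients per part is a pragmatic choice, with no alpha, power or SD stated.

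**Inputs from the protocol.** N = 25 patients per part. In Part 1, J = 3 pEEG levels, with measurements averaged per level and three blood samples. The fixed and random effects are as described above.

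**Assumptions, none from the documents (Part 1).**
- Outcome scaled to a between-patient SD of 1, with intraclass correlation (ICC) 0.5–0.9. Residual variance is s² = (1 − ICC)/ICC.
- Between-patient SD of propofol effect-site concentration 0.8 µg/ml. Within-patient SD left after the pEEG level, sw, 0.15–0.5.
- rho is the correlation between a patient's mean propofol and that patient's mTc-MEP level, 0 to 0.5 in size.
- One propofol covariate at a time.

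**Step 1: the weight.** In the random-intercept model the single coefficient is approximately w·βW + (1 − w)·βB, where w = A/(A + B), A = (N − 1)(J − 1)sw²/s², and B = J(N − 1)(0.8² + sw²/J)/(s² + J).

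Take ICC 0.7 and sw 0.3, so s² = 0.3/0.7 = 0.4286:
- A = 24 × 2 × 0.09/0.4286 = 10.08
- B = 3 × 24 × 0.67/3.4286 = 14.07
- w = 10.08/24.15 = 0.417

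So 58% of the weight falls on the between-patient slope.

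**Step 2: the bias.**
- *No within-patient effect, rho −0.3.* βB = −0.3 × 0.8/0.67 = −0.358. Expected coefficient: 0.583 × (−0.358) = −0.209. Simulated mean: −0.226. This looks like suppression by propofol where none exists.
- *True within-patient effect −0.6, rho +0.3.* βB = 0.358 − 0.6 × 0.03/0.67 = 0.331. Expected coefficient: 0.417 × (−0.6) + 0.583 × 0.331 = −0.057. Simulated mean: −0.063. The real effect is almost cancelled.

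**Step 3: simulated test behaviour in Part 1** (REML, two-sided 5%, 2000 runs per cell).

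No within-patient effect, all nine combinations of ICC (0.5, 0.7, 0.9) and sw (0.15, 0.3, 0.5):

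| size of rho | single term rejects |
|---|---|
| 0 | 4.9–6.2% |
| 0.3 | 9–26% |
| 0.5 | 16–61% |

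With patient mean and deviation entered separately, the deviation term rejects in 4.1–5.9% across all cells.

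True within-patient effect −0.6:

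| ICC, sw, rho | single term: rejects, mean estimate | deviation term: rejects, mean estimate |
|---|---|---|
| 0.7, 0.3, 0 | 26.6%, −0.27 | 46.6%, −0.61 |
| 0.7, 0.3, 0.3 | 9.6%, −0.06 | 45.6%, −0.60 |
| 0.5, 0.3, 0.5 | 26.6%, +0.28 (wrong sign) | 23.5%, −0.62 |
| 0.9, 0.5, 0.3 | 99.7%, −0.51 | 100%, −0.60 |

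The last row shows that the harm fades when within-patient variation is ample and residual noise small. Monte Carlo error is at most about 1.1 points.

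**Step 4: pEEG in Part 2** (16 readings, random intercept and MAP slope, assumed between-patient pEEG SD 3, no within-patient pEEG effect, Wald test).
- Within-patient SD 1: single term 18.7% (ICC 0.5, rho 0.3) and 22% (ICC 0.7, rho 0.5), against 8% and 6.5% for the deviation term. At rho 0 the single term rejects in 9.3% and 8.5%, so part of the excess over 5% has nothing to do with mixing.
- Within-patient SD 3 (ICC 0.7, rho 0.5): 6.5% against 5%. No inflation.

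These cells have 200–300 runs, with error of about 1.5–3 points.

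**Step 5: where it does not apply.** The Part 1 pEEG target takes the same three values in every patient. Its patient mean is constant, so it has no between-patient part to mix in. MAP in Part 1 was not simulated; the algebra of step 1 is the argument there.

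**The case against.** **The objective is prediction.** This is the strongest reply. If patients who need more propofol have smaller mTc-MEPs, knowing the concentration does help predict absolute amplitude, and that gain is legitimate. This stands. A reader might infer that the within-patient effect is the declared target and that any other rejection is false. The documents do not say so: the baseline criterion is in the Background and defines no estimand for this objective. The reply does not cover the Part 2 hypothesis that MAP affects mTc-MEPs more than pEEG does, nor the stated use of judging a change in one patient.

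**Coding may be settled elsewhere.** The article does not say that covariates enter as raw values, and a fuller analysis plan may split them. Fair. But the article describes these models down to the residual distribution, and one term per covariate is the plain reading.

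**No coefficient test is stated.** True; the rejection rates describe a conventional 5% test, not a rule in the plan. The bias in the estimate does not depend on any test.

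**The study is hypothesis-generating, and age may be adjusted for.** Both are true and both limit the weight of the point. The age adjustment is optional, and other shared traits would remain.

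**Conclusion.** The concern holds in a limited form. As written, each added covariate has one coefficient that cannot be read as the effect of a change within a patient. It is strongest for propofol in Part 1, where under the assumed values a null within-patient effect is rejected in 9–26% (correlation 0.3 in size) to 16–61% (0.5) of trials, and a real effect can be masked. For pEEG in Part 2 it is smaller, and it disappears when pEEG varies enough within patients. It does not arise for the pEEG target in Part 1.

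The size rests on correlations and variances that the documents do not give. When patient means are unrelated to the patients' mTc-MEP level, the test of a null effect in Part 1 keeps about its nominal size.

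A reader might infer that the secondary conclusions are invalid as a whole. The documents do not support that. A comparison of overall predictive value can stand; what fails is reading the individual coefficients as within-patient effects.

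**What to change.** In both Secondary outcome paragraphs of Statistical methods, enter each measured covariate as two terms: the patient's mean and the deviation from that mean at each reading. This applies to propofol effect-site concentration, plasma concentration, and MAP (Part 1) or pEEG (Part 2). Plasma deviations exist only at the three sampled levels, so in Part 2, with mTc-MEPs every 2 minutes, the plasma term must be confined to those levels. The random effects and residual structure stay as written.

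Keep the overall model comparison as the answer to the prediction objective. Report the within-patient and between-patient coefficients separately. Base two kinds of statement on the deviation terms: those about interpreting an amplitude fall from baseline, and the Part 2 comparison of the pEEG effect with the MAP effect.

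The single-term model is the special case in which the two coefficients are equal, so nothing in the written plan is lost. The cost is a sentence or two and a few derived columns, with no new data or procedures. The downside is one extra coefficient per covariate and a wider interval for the within-patient effect where a covariate varies little within patients.
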